## Abstract

**Background:**

Cutaneous T-cell lymphoma (CTCL) is a rare group of lymphomas that primarily affects the skin. Mycosis fungoides (MF) is the most common form of CTCL and Sézary syndrome (SS) is more infrequent. Early stages (IA-IIA) have a favorable prognosis, while advanced stages (IIB-IVB) have a worse prognosis. Around 25% of patients with early stages of the disease will progress to advanced stages. Malignant skin-infiltrating T-cells in CTCL are accompanied by infiltrates of nonmalignant T-cells and other immune cells that produce cytokines that modulate the inflammation. Skin infection, often with *Staphylococcus aureus,* is frequent in advanced stages and can lead to sepsis and death. *S. aureus* has also been reported to contribute to the progression of the disease. Previous reports indicate a shift from Th1 to Th2 cytokine production and dysfunction of the skin barrier in CTCL. Treatment response is highly variable and often unpredictable, and there is a need for new predictive and prognostic biomarkers.

**Objective:**

This prospective translational study aims to identify prognostic biomarkers in the blood and skin of patients with MF and SS.

**Methods:**

The Predictive and Prognostic Biomarkers in Patients With MF and SS (BIO-MUSE) study aims to recruit 120 adult patients with MF or SS and a control group of 20 healthy volunteers. The treatments will be given according to clinical routine. The sampling of each patient will be performed every 3 months for 3 years. The blood samples will be analyzed for lactate dehydrogenase, immunoglobulin E, interleukins, thymus and activation-regulated chemokine, and lymphocyte subpopulations. The lymphoma microenvironment will be investigated through digital spatial profiling and single-cell RNA sequencing. Microbiological sampling and analysis of skin barrier function will be performed. The life quality parameters will be evaluated. The results will be evaluated by the stage of the disease.

**Results:**

Patient inclusion started in 2021 and is still ongoing in 2023, with 18 patients and 20 healthy controls enrolled. The publication of selected translational findings before the publication of the main results of the trial is accepted.

**Conclusions:**

This study aims to investigate blood and skin with a focus on immune cells and the microbiological environment to identify potential new prognostic biomarkers in MF and SS.

**Trial Registration:**

ClinicalTrials.gov NCT04904146; https://www.clinicaltrials.gov/study/NCT04904146

**International Registered Report Identifier (IRRID):**

DERR1-10.2196/55723

## Introduction

### Mycosis Fungoides and Sézary Syndrome

Cutaneous T-cell lymphoma (CTCL) is a rare group of lymphomas that primarily affects the skin [1-3]. The pathogenesis of CTCL is not yet fully understood [3]. The annual incidence of CTCL is 0.7 per 100,000. Mycosis fungoides (MF) is the most prevalent form and comprises 60% of CTCL, with a higher male incidence (1.6:1.0) and a peak age incidence between 50 and 74 years [4]. Since MF often has a chronic course, its prevalence is considerably higher. The skin lesions in MF can be patches, plaques, tumors, or erythroderma. Sézary syndrome (SS) is an aggressive leukemic variant of the disease and constitutes only 5% of CTCL; it is defined as a triad of erythroderma, lymphadenopathy, and the presence of neoplastic T-cells in peripheral blood [5]. The extent of the disease in the skin is measured according to the Modified Severity-Weighted Assessment Tool [6,7]. Both MF and SS are staged according to the same tumor-node-metastasis-blood (TNMB) classification, assessing the involvement of skin, peripheral lymph nodes, peripheral blood, and visceral organs [8].

### Prognosis of MF and SS

The TNMB stage at diagnosis remains the most important prognostic factor [9,10]. Many patients with early stages of MF have an indolent disease with a 5-year disease-specific survival of 89% to 98% [8,11]. However, approximately 25% of patients with early stages of disease will later progress to advanced stages [4]. Patients with advanced stages of MF have a 5-year disease-specific survival of 18% to 56% associated with treatment failure [8,10]. The 5-year disease-specific survival of SS is 36% [3,8,10].

Multivariate analyses of cohorts of patients with MF and SS have identified potential adverse prognostic factors in the early stages of disease consisting of male gender, aged >60 years, plaques, folliculotropic disease, and stage N1/NX and negative prognostic factors for advanced disease consisting of male gender, aged >60 years, stages B1/B2 and N2/N3, and visceral involvement [12,13]. The presence of plaque lesions in the early stage of the disease, large cell transformation in the skin, and elevated lactate dehydrogenase are also identified as adverse prognostic factors [11,14,15]. Still, there is an unmet clinical need to identify which patients will progress to an advanced stage of disease, and there is a great need for new reliable prognostic markers.

### Treatments for MF and SS

The therapeutic options for MF and SS range from skin-directed therapy (SDT) to systemic treatment, and the selection of appropriate treatment is primarily based on the stage of the disease. There are only a few randomized controlled trials for the treatment of MF and SS, and current recommendations for treatment are mainly based on consensus meetings and international guidelines [4,5,10]. The treatment of the early stages of MF aims at modulating the immune response in the skin through SDT, such as topical corticosteroids and UV light therapy. Local radiation therapy usually has a good effect in all stages. In early stages that are refractory to SDT or in advanced stages, systemic treatment is used, including retinoid derivatives, low-dose methotrexate, and interferon alfa. In patients with lymphoma cells expressing CD30, targeted chemotherapy with brentuximab vedotin can be used. Further, standard chemotherapy such as gemcitabine or doxorubicin can be used; however, this often results in only short remission periods. Extracorporeal photopheresis can be used in erythrodermic stages of MF and SS and mogamulizumab and alemtuzumab can be used in advanced stages of disease. Highly selected patients with advanced stages of disease can be considered for allogeneic stem cell transplantation. Histone deacetylase (HDAC) inhibitors such as vorinostat and romidepsin are approved by the US Food and Drug Administration but are not commonly used in Europe [16,17]. Total skin electron beam therapy can be used in widespread disease in the skin or before allogeneic stem cell transplantation. Treatment response is unpredictable, and there is an unmet clinical need to find reliable predictive markers.

### Immunological Changes of the Microenvironment of CTCL in Skin and Blood

Early stages of CTCL derive from mature CD4+ T-cells, or rarely CD8+ T-cells, in the skin. The restriction to the skin suggests that the affected cells are dependent on the specific cutaneous microenvironment, including cytokines and adhesion molecules. Malignant skin-infiltrating cells are accompanied by infiltrates of nonmalignant T-cells and other immune cells. The infiltrating benign immune cells produce a variety of cytokines that modulate cutaneous inflammation and are important constituents of the local environment of the tumor, fostering proliferation, survival, and migration [3]. Attempts to associate a unique cytokine profile of the disease based on skin or blood samples have indicated that a shift from Th1 to Th2 cytokine production accompanies disease progression [18,19], but the mechanisms behind this shift are not completely known [20]. In the advanced stages of the disease, a reduction of skin-infiltrating CD8+ T-cells has been observed, as well as a shift toward M2 polarized macrophages and increased frequencies of NK cells and B-cells [21,22]. Other major immunological changes also facilitate the environment of the lymphoma cells and impair the host immunological defense [22]. The hypothesis of this study is to further explore these immunological changes through analysis of lymphocyte subpopulations in blood and skin together with cytokine expression in plasma through protein array analysis. We also hypothesize that we will detect other cells, molecules, and factors in the microenvironment of the tumor that could influence the clinical course of CTCL.

### Epigenetic Modifications in CTCL

Regulation of DNA transcription is complex, and the mechanisms of regulation of DNA transcription in CTCL are partially unknown. HDACs can regulate the expression of genes and activities of transcription factors involved in malignant transformation and immune defense. HDACs act mainly through alteration of the structural components of chromatin by histone deacetylation, thus affecting the 3D conformation of DNA without changing or interrupting its sequence. Epigenetic drugs such as HDAC inhibitors have shown promising results in patients with advanced disease, emphasizing the impact of epigenetic regulators on the disease. Based on phase II data demonstrating long-term remission in 35% of heavily pretreated patients, HDAC inhibitors have been approved by the US Food and Drug Administration for second-line treatment of CTCL [16,17]. Although the dysregulated function of HDAC inhibitors may have an important role in malignant transformation and in the response to cancer treatment, the in vivo mechanisms behind the effects of HDAC inhibitors in CTCL are largely unknown. However, next-generation sequencing data have shown amino-acid or copy number alterations of 13 chromatin modifiers in 1% to 7% of CTCL cases, respectively, suggesting a mutation-driven epigenetic imbalance in CTCL [23]. Interestingly, HDAC inhibitors have been shown to reprogram the epigenome of host nonmalignant T-cells toward normal patterns, emphasizing the role of the host T-cells for therapy response [24,25].

### Microbiological Changes and Skin Barrier Function in MF and SS

Skin infections, often with *Staphylococcus aureus*, are frequently seen in advanced stages of MF and SS. In patients who are immunocompromised, skin infections can lead to sepsis and death. Some studies indicate that a shift from Th1 to Th2 cytokine production and dysfunction of the skin barrier contribute to skin infections [26,27]. The underlying basis for the microbiological changes and the skin barrier function in CTCL need to be further elucidated for their potential role in the pathogenesis and progression.

### Goals of This Study

The primary objective of this study is to identify serum-protein markers for 6-month progression-free survival (PFS) and to identify the immune cell profile in blood for 6-month PFS.

Secondary objectives are to identify the immune cell profile in the skin for 6-month PFS, analyze the lymphoma microenvironment in the skin for 6-month PFS, identify the skin barrier and skin microbiology profiles for 6-months PFS, and identify the epigenetic changes in lymphoma T-cells and host T-cells for 3 months PFS.

## Methods

### Study Design

The Predictive and Prognostic Biomarkers in Patients With MF and SS (BIO-MUSE) study is a translational prospective study, aiming to include 120 adult patients with MF and SS and a control group of 20 healthy volunteers (Figure 1). Sampling of each patient will be performed every 3 months for 3 years. The control group will be examined on 3 different occasions at least 2 months apart. This study is presently open at Skåne University Hospital and aims to open at Karolinska University Hospital. The multicenter study design enables other Swedish sites to be included, after further ethical approval.

**Figure 1 figure1:**
[figure not shown]
Study design of the BIO-MUSE study. BIO-MUSE: Predictive and Prognostic Biomarkers in Patients With Mycosis Fungoides and Sézary Syndrome; CT: computed tomography; DLQI: Dermatology Life Quality Index; IgE: immunoglobulin E; IL-6: interleukin-6; IL-8: interleukin-8; IL-10: interleukin-10; IL-1beta: interleukin-1beta; LDH: lactate dehydrogenase; MF: mycosis fungoides; mSWAT: Modified Severity-Weighted Assessment Tool; NRS: Numerical Rating Scale; sIL-2R: soluble interleukin-2 receptor; SS: Sézary syndrome; TARC: thymus and activation-regulated chemokine; TEWL: transepidermal water loss; TNMB: tumor-node-metastasis-blood.

### Ethical Considerations

This study’s protocol is written per the Declaration of Helsinki and the International Council for Harmonisation’s good clinical practice guidelines. This study was registered with ClinicalTrials.gov (NCT04904146) and approved by the Swedish Ethics Committee (2019-05130). Written informed consent will be obtained from participants according to the Declaration of Helsinki and International Council for Harmonisation’s good clinical practice guidelines.

### Eligibility Criteria

Inclusion criteria will be patients aged 18-100 years with histologically confirmed MF and SS (stage IA-IVB) and World Health Organization performance status 0-3. The inclusion criteria for the healthy control group will be healthy adults aged 18-100 years with World Health Organization performance status 0-2 and the absence of any malignant, autoimmune, or infectious disease. The exclusion criteria for both groups are psychiatric illnesses or conditions that could interfere with the ability to understand the requirements of this study.

### Stage of Disease and Modified Severity-Weighted Assessment Tool

Patients will be staged according to the TNMB classification [8]. The extent of disease in the skin will be measured according to the Modified Severity-Weighted Assessment Tool [6,7]. Progression or regression will be defined as a shift from one stage to another.

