## Results

Patient inclusion started in 2021 and is still ongoing in December 2023, with 18 patients and 20 healthy controls enrolled. Until December 2023, a total of 2 included patients have declined further participation due to the extra visits in this study. Further, 2 patients have died from MF during this study. The publication of selected translational findings before the publication of the main results of the trial is accepted, and data analysis is in progress.

The evaluation of the stage of the disease will be observed every 3 months according to the TNMB classification, where the shift from one stage to another implies progression or treatment response. After the study, patients will be grouped as either early stage of the disease (IA-IIA) or advanced stage of the disease (IIB-IVB). The patients crossing over from the early stage of the disease to the advanced stage of the disease group will be analyzed both individually and as a group. Approximately 30% (36/120) of patients are estimated to be in the advanced stage of the disease group. The translational samples in the early stage of the disease group will be compared to samples from the advanced stage of the disease group. The treatments directed against MF are documented throughout this study. Excluded patients will be presented along with the final results. Depending on patient numbers, treatment data will be presented descriptively, or if possible, to support data on treatment predictive biomarkers.

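### Treatment response is defined only as a change of TNMB stage, so improvement within a stage is not counted and the chance of a recorded response depends on entry stage

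*Protocol article*

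**What the plan says.** In the protocol article, Methods, Stage of Disease and Modified Severity-Weighted Assessment Tool, patients are staged by TNMB and "The extent of disease in the skin will be measured according to the Modified Severity-Weighted Assessment Tool". The sentence that follows gives the outcome rule: "Progression or regression will be defined as a shift from one stage to another". The Results section restates it for the three-monthly stage evaluation, "where the shift from one stage to another implies progression or treatment response". No other criterion for response appears in the article.

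Eligibility Criteria admits patients with "histologically confirmed MF and SS (stage IA-IVB"), so IA is the lowest stage that the article lists. The Results section gives the use to which response might be put: "Depending on patient numbers, treatment data will be presented descriptively, or if possible, to support data on treatment predictive biomarkers". The Discussion (Principal Findings) and the Conclusions both name predictive biomarkers as an aim, next to prognostic ones. The primary and secondary objectives in Goals of This Study are all worded in terms of progression-free survival (PFS).

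**The concern.** A stage is a broad category. A patient's skin disease can shrink a good deal without a change of stage, and under the stated rule that change is not a response. In IA the limit is absolute for anything short of clearance, because the eligible range lists nothing lower. Patients in higher stages can at least be recorded as responders by moving down.

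Two things follow for a treatment-predictive analysis. First, true responders in IA join those without a recorded response, and this dilutes any marker that really separates the two. Second, recorded responders come disproportionately from higher stages, so a marker that tracks only stage can appear to predict response. The second effect matters here because the study's main planned comparison is early against advanced stage, and markers that differ by stage are what it expects to find.

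**Working it through.** **Text check.** Both statements of the rule (Methods and Results) name stage shift and nothing else. mSWAT appears in the same Methods section but not in the rule. This is a rule that the article fixes, not a detail left to a fuller document.

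**Figure in the article.** "Approximately 30% (36/120) of patients are estimated to be in the advanced stage of the disease group". Check: 0.30 × 120 = 36, which reproduces. The early group (IA-IIA) is then 120 − 36 = 84.

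**Assumptions, none of them from the article.** IA share of the early group 30% to 60%; true response rate 40% in every stage; every true responder outside IA is recorded (this favours the stated rule); a marker that differs by 0.55 SD between true responders and non-responders; a two-sided Mann-Whitney test at 5% of recorded responders against the rest. The article does not specify that comparison.

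**Patients affected.** 0.30 × 84 ≈ 25 and 0.60 × 84 ≈ 50, which is 21% and 42% of 120.

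**Recorded response rate.** If a fraction c of IA responders clear and are counted, the recorded rate is 0.40 × [1 − (1 − c) × n(IA)/120].
- c = 0: 0.40 × (1 − 25/120) = 31.7%; 0.40 × (1 − 50/120) = 23.3%.
- c = 0.5: 0.40 × (1 − 12.5/120) = 35.8%; 0.40 × (1 − 25/120) = 31.7%.

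**Simulation with N = 120.** The false-positive columns use a marker unrelated to response but 0.8 SD higher in the 36 advanced-stage patients.

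| Label | Power, 25 in IA | Power, 50 in IA | False positives, 25 in IA | False positives, 50 in IA |
|---|---|---|---|---|
| True response | 81% | 81% | 5% | 5% |
| Stage shift, no IA responder clears | 66% | 47% | 7% | 16% |
| Stage shift, half of IA responders clear and are counted | 74% | 65% | 5% | 7% |

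Repeat runs differ by one or two percentage points. The direction of the power loss is the same throughout. Its size depends heavily on c and on the IA share. The false-positive problem nearly disappears if half of the IA responders clear and are counted.

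**The case against.** The strongest case against is that response is not an endpoint here. Every objective concerns PFS. The Statistical Analysis section plans principal component analysis and Mann-Whitney tests between early and advanced stage, descriptive statistics, and Kaplan-Meier plots. It contains no comparison of responders with non-responders. The one planned use of treatment data depends on patient numbers, and 18 patients were enrolled by December 2023. All of this stands, and it limits the reach of the point. It does not remove the point, because predictive biomarkers are a declared aim and the article fixes the label on which such work would rest.

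It is also fair to say that the power figures rest on invented inputs and describe a test that the article does not plan. They show direction and plausible scale, not an estimate for this study.

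Two stronger readings are tempting and are not supported:
- A reader might infer that a patient whose disease clears drops out of both the early and the advanced group. The article does not say so. It says "After the study, patients will be grouped as either early stage of the disease (IA-IIA) or advanced stage of the disease (IIB-IVB"), without stating which stage decides, so a cleared patient could keep the group of the entry or worst stage. Silence on this in a condensed article is not an error.
- A reader might quote only the worst-case figures, 47% power and 16% false positives. They assume that no IA responder ever clears, which nothing in the article supports.

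**Conclusion.** The point holds within limits. As worded, the rule misses improvement within a stage, and for IA patients it misses any improvement short of clearance. Response is therefore under-counted and its recording is tied to entry stage. That conclusion needs only the article's own wording and its eligible stage range.

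The downward-shift problem does not affect the PFS objectives. It affects the conditional treatment-predictive biomarker work.

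The documents do not support a size, since they give neither the IA share nor a response rate. Under the assumptions listed above, power falls from about 81% to between 74% and 47%, according to how many patients are in IA and how many of the IA responders clear.

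**What to change.** Change the wording in both places where the rule appears (Methods, Stage of Disease and Modified Severity-Weighted Assessment Tool; and Results):

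1. Keep stage shift for progression and for response in blood, nodes or viscera. Dropping it altogether would lose responses seen mainly outside the skin, and Sézary syndrome and stages up to IVB are eligible.
2. Add a prespecified criterion based on change in mSWAT from its value at the start of the documented treatment, so that improvement within a stage counts as response. The article gives no threshold; the sponsor should choose one from its response criteria and state it before the data are analysed.
3. State that clearance counts as response.
4. Use entry stage as a covariate or stratum in any treatment-predictive marker analysis.

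The cost is a little more analysis and a composite response label, which is somewhat harder to describe than a single rule. mSWAT, stage and treatment are already recorded, so no new visit or procedure is needed. With 18 of 120 patients enrolled at the article's last count, the label can still be settled before the main analysis.

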### Statistical Analysis

The sample profiles from patients with an early stage of disease (stage IA-IIA) will be compared to samples from patients with an advanced stage of disease (stage IIB-IVB) using multivariate analysis with principal component analysis. Individual samples will be compared between the groups using the Mann-Whitney *U* test. Other translational samples will be presented by descriptive statistics. Progression-free and overall survival will be presented using Kaplan-Meier plots.

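### Progression is defined only as a change of TNMB stage, so a patient entering in stage IVB cannot register progression and worsening within a stage counts as progression-free

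*Protocol article*

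**What the plan says.** The protocol article fixes the rule under Stage of Disease and Modified Severity-Weighted Assessment Tool: "Progression or regression will be defined as a shift from one stage to another". The Results section repeats it for the 3-monthly TNMB assessments, "where the shift from one stage to another implies progression or treatment response". No other criterion for progression appears.

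The same Methods section also says: "The extent of disease in the skin will be measured according to the Modified Severity-Weighted Assessment Tool". No change in that score is linked to progression.

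Under Goals of This Study, the primary objective covers serum proteins and the blood immune-cell profile, both for 6-month PFS. All secondary objectives are for PFS too, at 6 months or, for the epigenetic changes, at 3 months. Eligibility Criteria admit "histologically confirmed MF and SS (stage IA-IVB"), that is, the whole range. On analysis, the article says "Progression-free and overall survival will be presented using Kaplan-Meier plots". It does not list the events that make up PFS.

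**The concern.** The progression rule decides which patients count as having worsened, and every marker is to be judged against that outcome. A rule that needs a move to a higher stage has two blind spots. It cannot register worsening in a patient who is already at the top of the eligible range. It also ignores worsening that stays inside one stage, even though the study collects a measure of skin extent that could show it.

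What is at stake is the classification of patients in the primary endpoint. Patients who worsened would sit in the progression-free group. The first blind spot affects only the most advanced patients, so the error is not spread evenly over the cohort.

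**Working it through.** **Inputs.** The progression rule (Stage of Disease section, repeated in Results); eligibility IA to IVB (Eligibility Criteria); 120 patients (Study Design); the expected advanced-stage share, "Approximately 30% (36/120) of patients are estimated to be in the advanced stage of the disease group" (Results).

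**Step 1, the article's own figure.** 0.30 × 120 = 36, which agrees with the article. The early group is then 120 − 36 = 84.

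**Step 2, apply the rule as written.**

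| Stage at entry | What happens | Recorded as |
|---|---|---|
| Below IVB | Stage rises | Progression |
| Below IVB | Skin disease worsens, stage unchanged | Progression-free |
| IVB | Disease worsens by any amount | Progression-free |
| IVB | Stage falls | Regression |

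The third row follows from logic alone: IVB is the last stage in the eligible range, so no upward shift exists. The table concerns the progression part of PFS. If death counts as a PFS event, a patient in IVB can have an event by death, but not by progression.

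**Step 3, what would be needed to size it.** For patients entering in stage s, let n be their number, r the true probability of worsening by 6 months, and q the share of that worsening that comes with a rise in stage.

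- Recorded progression risk in stage s = r × q.
- Expected number of missed worsenings = sum over stages of n × r × (1 − q).
- In IVB, q = 0, so the recorded risk is r × 0 = 0 whatever r is.
- Below IVB, q lies between 0 and 1 and is not given.

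The article gives the total of 120 and the split of 84 and 36. It gives no n for IVB, and no r or q for any stage, so the sum cannot be evaluated. The only bound is that patients entering in IVB number between 0 and 36, if the estimate of 36 is right and is read as stage at entry.

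**Step 4, why dependence on stage matters.** Compare marker-high with marker-low patients:

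- Recorded risk ratio = (r_high × q_high) / (r_low × q_low) = true ratio × (q_high / q_low).

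The recorded ratio equals the true one only if q is the same in both groups. A marker that is higher in the most advanced disease puts more IVB patients, with q = 0, in the marker-high group. Other things equal, this pulls q_high / q_low below 1. The association is then understated and, with enough IVB patients, could be reversed. The study expects its profiles to differ by stage, since it plans to compare early with advanced patients, so this pattern is plausible here.

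**The case against.** **Stage is a coherent endpoint.** The introduction names as the unmet need the identification of patients who will move to advanced disease, and the results are to be grouped by stage. TNMB includes the skin, so some skin worsening does change the stage. Treatment follows clinical routine, and mSWAT may move with treatment changes. This stands as a reason to keep the stage shift as a component and as a sensitivity analysis. It does not answer the IVB problem, because the study admits all stages and sets PFS objectives for all of them.

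**No marker test on PFS is described.** Statistical Analysis names principal component analysis and Mann-Whitney comparisons of early with advanced stage; PFS appears only in Kaplan-Meier plots. This also stands, and it makes the effect on marker results less direct. Still, the objectives are to find markers for PFS, so markers must be set against PFS status at some point.

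**The article is condensed.** The full protocol or analysis plan may say more. That covers the handling of death. It does not cover the progression rule, which the article states as a definition and repeats.

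**A stronger reading about deaths.** A reader might infer that deaths are not events, the more so as the Results report: "Further, 2 patients have died from MF during this study". The documents do not support this. The quoted rule defines progression, not the PFS event; PFS ordinarily counts death; and nothing in the article censors deaths. The 2 deaths among 18 enrolled patients come without times, stages or prior staging, so they give no 6-month rate and do not show that any event was lost.

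Nor can the problem be sized by setting expected deaths against early-to-advanced shifts. That presumes deaths are left out, ignores shifts inside the early and advanced groups, and needs a time span for the 25% progression figure that the article does not give.

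**Conclusion.** The point holds in two parts: the rule cannot register progression in a patient who enters in IVB, and it counts worsening within a stage as progression-free although mSWAT is collected. Both follow from a rule that the article states and that governs every objective.

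A reader might go further and conclude that the endpoint misses much of the real progression. The documents do not support that, because they give no rate of worsening within a stage and no count of IVB patients. The size is unknown; the only bound is 0 to 36 patients entering in IVB, under the assumption stated above. What can be said is that the error depends on stage and so can bias marker-PFS associations rather than only add noise. This assumes that markers differ by stage and that they will be related to PFS as the objectives say.

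The correction is worth making because it is cheap and concerns the primary endpoint.

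**What to change.** Define the PFS event as the first of:

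1. a TNMB stage higher than at inclusion;
2. an mSWAT increase over the lowest prior value, beyond a threshold fixed before any marker data are read, and confirmed at the next visit;
3. death from any cause. The article does not state how death counts, so confirm this.

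State that patients entering in IVB contribute through (2) and (3). Say which date is used for a confirmed mSWAT increase, since with 3-monthly visits a rise first seen at month 6 would be confirmed only at month 9. Report the stage-shift-only version as a sensitivity analysis.

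**Cost.** An amendment of the endpoint wording. Stage and mSWAT are already recorded, and overall survival is already planned. The article gives the 3-monthly interval for staging and sampling but not expressly for mSWAT, so the amendment should confirm that mSWAT is scored at the same visits. With 18 of 120 patients enrolled in December 2023, most of the cohort could still be followed under the revised definition. Because the Results say that data analysis is in progress, the threshold should be fixed promptly.

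**Downside.** The composite event is less specific than a stage shift, and mSWAT can move with treatment changes. Confirmation at the next visit and the sensitivity analysis limit this but do not remove it.
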